
1. **RISKS AND DISCOMFORTS**
   1. Complications of surgical and non-surgical procedures, etc.

Obtaining a venous whole blood specimen (10 mL for adults, 4 mL for children) for testing by RT-PCR to determine if a person is infected with EBOV is currently standard of care. No additional blood samples will be drawn via venipuncture for study purposes. In parallel with venipuncture, an additional blood sample will be collected via fingerprick. Risks of blood drawing are typically minor, with a bruise at the puncture site being the most common risk. There is a very small risk of infection. Saliva (buccal swab) and/or urine specimens will also be collected if appropriate to the novel POC test; collection of these sample types is non-invasive. The person collecting study samples and performing the novel POC test will be wearing personal protective equipment (PPE) identical to that used for venipuncture to collect whole blood for clinical purposes. Fingerpricks will be performed with safety lancets (spring-loaded). All healthcare workers and study personnel participating in the research will be required to use personal protective equipment as directed by the standard operating procedures at each participating facility.

**The risk to phlebotomy/research teams will be minimized by the use of personal protective equipment as per Standard Operating Procedures.**

- 1. Drug side effects and toxicities

Participation in this study will not increase participants’ exposure to drug side effects or toxicities.

- 1. Device complications/malfunctions

Participation in this study will not increase participants’ exposure to device complications or malfunctions; the novel POC devices do not touch the patient, and results of novel POC tests will not be used for clinical management.

Psychosocial (non-medical) risks

The primary non-medical risk is a breach in confidentiality, resulting in the disclosure of patient information. Careful attention will be paid to maintaining confidentiality of all paper documents, electronic data, and biological specimens. Participants will each be assigned a unique ID code, which will be linked to their name in either a hard copy log stored in a locked cabinet or a password-protected form stored on an encrypted study computer. This code will be used in lieu of participants’ names on all hard copy forms, electronic datasets and biological specimens. Any paper records will be stored in a locked cabinet, and all electronic data will be password protected.

This project will observe all of the privacy and security requirements outlined by the Health Insurance Portability and Accountability Act (HIPAA) of 1996. All personally identifiable data for this study will be maintained and stored only at the participating PIH Sierra Leone sites, and study personnel will be responsible for ensuring the personal de-identification of core data needed for carrying out the study. Specifically, for all study subjects at the PIH sites, our data collection process is outlined as follows:

- 1. Verbal consent is obtained by study personnel. An informed consent log will document study subjects who verbally consent to enroll in the study.
  2. A study identification number is assigned to the enrolled subject. This ID number will be used in lieu of subjects’ names on all study materials. The key to this ID number will be stored in a locked cabinet or in a password-protected file on an encrypted computer, only accessible to study staff.
  3. Research fingerprick blood, saliva/buccal swab, and/or urine samples are collected by designated trained health care workers, labeled with their previously assigned study identification number, and tested with the novel POC test per SOP. Any images of resulted tests (e.g. lateral flow tests) will be marked only with study ID number. Data input for Instrument-based diagnostics will include study ID number only (no patient identifiers).
  4. Venipuncture blood collected for clinical testing (RT-PCR) in the reference laboratory will be labeled with personal identifiers per clinical routine. The tube will also be labeled with the assigned study identification number for later use for de-identification of excess whole blood in the reference laboratory (for testing with the novel POC test in the reference laboratory). Study staff will follow up on the clinical RT-PCR results that are returned to the PIH site per clinical routine. Ct values and results of POC tests performed in the reference lab will be collated by the reference lab and provided to study staff.
  5. Clinical and laboratory data (latter including results of POC testing with the novel test under study) are recorded by study personnel using separate clinical and laboratory data forms with no personally identifiable information; forms are labeled only with study identification number. Data will be subsequently entered into a database which similarly excludes all personally identifiable information. Copies or photographs will be made of the clinical and laboratory results forms in order to preserve this data and allow database data confirmation to be performed at a later time by study personnel.

Personally identifiable information will not be collected at any level for those subjects choosing not to participate in the study. All personally identifiable data volunteered by participants will be disassociated with the core response data prior to entry into the database. Publications or reports using the data collected in this study will only be reported or published in aggregate form with generalized results. This data collection process complies with HIPAA 45 CFR part 46.

- 1. Radiation risks

Participation in this study will not increase participants’ exposure to radiation.

1. **POTENTIAL BENEFITS**
   1. Potential benefits to participating individuals

There will be no direct benefit to subjects from this research. All study personnel will be made aware that the novel POC tests under study are for research purposes only and cannot be used to determine whether or not to initiate treatment, nor for any other clinical management decisions. There will be no payment for participation in this research study. There will be no costs to the subject for participating in this research study.

- 1. Potential benefits to society

As discussed above, development of EBOV POC tests will improve treatment of EBOV disease, facilitate studies to understand its prevalence and natural history, and ultimately lead to effective vaccines and therapies.

1. **MONITORING AND QUALITY ASSURANCE**
   1. Independent monitoring of source data

Clinical site coordinators will maintain Study Site Binders that include the Informed Consent script to be read to the patients, the approved Study Protocol, copies of the IRB and Ethics Committees approvals, and copies of the medical investigators’ CVs & Licenses. The study site coordinators and on-site medical investigators conduct regular study reviews following the Site Monitoring Protocol, when possible. During these reviews Consent and Enrollment are audited and logged and any Adverse Events or Protocol Deviations are investigated and recorded.

Data collected at the study site includes completed paper forms and electronic text and images (including automated POC test laboratory data). Study samples remaining after testing will be stored for repeat testing (if required) to resolve discordant results, and for future use in evaluations of novel diagnostics for EVD and other infectious diseases relevant to the differential diagnosis of EVD. All paper forms and electronic images will be maintained by study personnel. The limited data maintained at Harvard will include the digital database, copies of the de-identified primary data collection forms, and primary laboratory data for the novel POC tests (for platforms which store data). The database will be transmitted to the Harvard location electronically using a secure file sharing application. Study data will be maintained by study personnel on password-protected computers and transmitted to the Harvard site using password-protected, encrypted computers. Deidentified laboratory data (for automated POC tests) may also be transmitted securely via cloud-based technology for analysis by study personnel or the test manufacturer. The database, any scanned electronic forms, and raw laboratory data will be backed up regularly using password-protected, encrypted external hard drives. All host computers for study personnel with access to the study data will be password-protected and equipped with approved firewalls and antivirus software. Compliance to these data security safeguards will be ensured by requiring all project personnel to complete the NIH Computer Security Awareness Training Course or equivalent. Novel POC test manufacturers will be provided with copies of deidentified study data for product development purposes.

Samples will be logged and sequentially numbered at each site. The consent log/study ID key will be the only documentation containing patient names and other confidential information. This document will either be stored in a locked cabinet (if in hard copy) or will be password-protected and stored in an encrypted computer that will be kept in Sierra Leone. Samples and data will be identified by site and sequential number.

All data generated in this study, absent any personally identifiable information, may be sent to outside collaborators for further analysis. At the end of the study, all data and study forms will be stored for a minimum of five years at a secure location.

- 1. Safety monitoring

This study does not require a DSMB.

- 1. Outcomes monitoring

As results of novel POC tests will not be used for clinical management, this study will have no impact on clinical outcomes.

- 1. Adverse event reporting guidelines

We do not anticipate any adverse events to occur as a result of participation in this study. We will comply with the terms outlined in the PHRC guidelines on reporting unanticipated problems and adverse events. Unexpected events or occurrences will be immediately reported to the Principal Investigator, who will immediately notify PHRC and the local Research Ethics Committees. All unanticipated problems and adverse events will be reported within 7 calendar days of the date the principal investigator first becomes aware of the problem.

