Samples will be collected by fingerprick, buccal swab, and/or standard urine collection techniques for POC testing, as appropriate to the novel POC test under evaluation. Venipuncture samples will be collected in parallel for confirmatory testing at a central reference laboratory (below), per clinical routine at the selected PIH site. Verbal consent will be obtained from all subjects whose samples will be used for POC testing.

1. Central Reference Laboratory

A. Pilot discarded/excess specimen study: Prior to initiation of POC testing, the designated central reference laboratory participating in the substudy will perform a brief and focused evaluation of the novel rapid test using a limited number of discarded/excess venipuncture whole blood specimens in order to confirm that performance of the novel rapid test meets expectations. Specifically, whole blood specimens sent to this laboratory for testing by RT-PCR per clinical routine will also be used to test the novel POC test in parallel. These specimens will come from multiple clinical sites. After RT-PCR testing is performed per clinical routine, excess whole blood specimen will be de-identified and used for the rapid POC test, allowing direct comparison of results of testing by RT-PCR and the novel POC test. Consent will not be obtained for use of these specimens.

B. Clinical substudy: In parallel with POC testing, confirmatory testing of venipuncture blood will be performed at a designated central reference laboratory by benchmark RT-PCR, per clinical routine at the selected PIH site. These RT-PCR results will be used for clinical management, as per existing clinical routine. After RT-PCR testing is performed, excess whole blood specimen will be de-identified and used for testing with the POC test in the reference laboratory.

Note: Our current designated reference laboratory for the Port Loko PIH sites is the PHE laboratory in Port Loko, and for the Kono PIH sites will be a reference laboratory furnished by the Dutch government that will be operative in Koidu Town in mid-late January 2015 (with analytic protocols for EBOV detection that closely resemble those of PHE). Details regarding reference lab utilization of discarded (deidentified, excess) clinical specimens are being discussed with the WHO/FIND leadership (EDAC) and reference lab leadership, and will also be discussed with the Laboratory Technical Working Group and Surveillance Pillars in Sierra Leone.

- 1. Drugs to be used

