This project will not involve additions or changes to therapeutic regimens. Results of novel POC tests will not be used for clinical management.

- 1. Devices to be used

A. ReEBOV^TM^ Rapid Diagnostic Test

i. Description. The ReEBOV^TM^ Rapid Diagnostic Test (Corgenix, Broomfield, CO) is a recombinant Lateral Flow Immunoassay (LFI) for detection of the EBOV VP-40 protein in whole blood.

The ReEBOVTM Antigen Rapid Test is performed as a dipstick immunoassay. Whole blood (fingerprick or venous collection) is added to the sample pad and the dipstick is then added to a test tube containing sample buffer, which initiates flow of sample through the reagent pads and across the nitrocellulose membrane. As the assay develops, EBOV VP40 antigen forms immune-complexes with anti-EBOV VP40 polyclonal antibody gold conjugate. As these complexes are captured by the anti-EBOV VP40 polyclonal antibody Test Line, the deposition of the gold nanoparticles generates a pink to red signal which corresponds to the concentration of EBOV VP40 antigen in the sample. Excess gold-conjugate is captured by the Control Line, indicating a valid result. Visual interpretation is made after 5 to 15 minutes of development time.

ii. Analytical performance data. During preliminary evaluation against stored serum specimens in Kenema, Sierra Leone, the ReEBOV^TM^ Rapid Diagnostic Test demonstrated good agreement with the comparator method (CDC PCR assay as previously described[^11^](#_ENREF_11)). The rapid test gave 91% agreement with PCR-positive specimens and 93% agreement with PCR-negative specimens in 83 total specimens. The positive predictive value was 93%, while the negative predictive value was 91%. Signal range (band intensity) and uniformity were satisfactory.

The test was subsequently optimized to improve specificity; updated performance data is not currently available as the test is undergoing review for FDA Emergency Use Authorization (EUA) approval.

iii. Sample types to be tested at POC: capillary whole blood (fingerprick)

B. GeneXpert Ebola

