For consented study subjects, following testing of venous blood by RT-PCR per clinical routine, the reference laboratory will test excess venous whole blood with the novel POC assay under evaluation, as a control. Enrolled patients will have received a study number (G-####) at the time of enrollment to de-identify their laboratory samples and clinical data; after clinical testing, excess venipuncture blood sample will be de-identified, labeled with the associated study number, and tested with the novel POC assay. Depending on workflow in the reference laboratory, testing of the excess whole blood sample with the novel POC test may be performed either before, during, or after the RT-PCR testing; regardless, operators performing the novel POC assay will be blinded to the results of RT-PCR testing. If staffing and workflow allow, operators performing the RT-PCR testing will be blinded to the results of the POC test. Patients will be diagnosed based on RT-PCR results and clinical signs and symptoms by their treating physician; results of novel POC tests will not be used for clinical management. Excess whole blood specimen remaining after testing on the novel POC test will be stored for future use in evaluations of novel diagnostics for EVD and other infectious diseases relevant to the differential diagnosis of EVD.

Note: if case loads at each participating PIH clinical site are dropping rapidly (threatening study completion), we will consider testing the research samples collected an de-identified at POC (fingerstick blood, saliva/buccal swab, and/or urine) with the novel POC test in the reference lab, rather than at POC, for novel POC tests which allow sample transport. If this option is utilized, sample transport will meet all biosafety considerations applied to transport of clinical venipuncture samples.

1. **BIOSTATISTICAL ANALYSIS**
   1. Specific data variables being collected for the study

To support validation of assay performance, we will collect focused clinical and laboratory data for each participant (using designated data collection forms), to include:

Clinical Data: Age, sex, symptoms, number of days symptomatic at the time of testing, survival (for pilot discarded/excess specimen testing in the reference laboratory, only age and sex will be recorded).

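### Reference RT-PCR is blinded to the laboratory POC result only when convenient, and the POC test may be run first, so borderline reference calls can be made with that result known

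*Protocol*

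**What the plan says.** **Blinding.** Under Study Procedures (Data to be collected and when the data is to be collected), blinding in one direction is firm: "regardless, operators performing the novel POC assay will be blinded to the results of RT-PCR testing". In the other direction it is conditional: "If staffing and workflow allow, operators performing the RT-PCR testing will be blinded to the results of the POC test". The pilot description under Biostatistical Analysis (Power analysis) repeats the conditional wording.

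**Order of the two laboratory tests.** Division of testing activities, Central Reference Laboratory, Clinical substudy, puts RT-PCR first: "After RT-PCR testing is performed, excess whole blood specimen will be de-identified and used for testing with the POC test in the reference laboratory". The data-collection section opens its account of consented subjects the same way: "following testing of venous blood by RT-PCR per clinical routine, the reference laboratory will test excess venous whole blood with the novel POC assay". Later in that paragraph it says that, depending on workflow, "testing of the excess whole blood sample with the novel POC test may be performed either before, during, or after the RT-PCR testing".

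**Role of RT-PCR.** It is the sole reference standard for sensitivity and specificity (Biostatistical Analysis, Specific data variables) and the result on which patients are managed (Central Reference Laboratory, Clinical substudy). POC results are kept out of care: "Results of novel POC tests will not be used for clinical management".

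**The concern.** If RT-PCR were always called and recorded before the laboratory POC test was run, conditional blinding would do no harm, because there would be no laboratory POC result to see. Allowing the POC test to run before or during RT-PCR opens the route, and the conditional blinding leaves it unguarded. I found no unconditional safeguard elsewhere in the protocol.

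The exposure falls on weak positives and discordant specimens, where the RT-PCR operator has some discretion: whether a late Ct is called positive, or whether a run is repeated. These few specimens largely determine the accuracy estimates. A reference call drawn toward the POC result turns a disagreement into an agreement. The resulting bias favours the POC test, is not reflected in the confidence interval, and does not shrink as more patients are enrolled.

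**Working it through.** **1. The passages side by side**

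| Item | Clinical substudy | Pilot |
| --- | --- | --- |
| POC operator blinded to RT-PCR | Always | Always |
| RT-PCR operator blinded to POC | If staffing and workflow allow | If staffing and workflow allow |
| Order of tests | RT-PCR first (Central Reference Laboratory; opening of the data-collection text), then any order (later in the same paragraph) | RT-PCR first (Central Reference Laboratory); possibly one after another on arrival (Power analysis) |

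One operator who runs the POC test first and RT-PCR second satisfies every current requirement, yet makes the reference call knowing the POC result.

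**2. Which results are exposed**

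- *Venous POC result: direct.* Specific Aims calls it a control, but Study endpoints includes it in the main validation of the test.
- *Pilot: direct.* Its results decide whether a test goes to the clinical sites (above 90%/90% expected, above 85%/85% considered).
- *Fingerprick tested in the laboratory: direct.* The data-collection section allows this if case loads fall.
- *Fingerprick tested at the site (Aim 1): indirect.* The laboratory sees the venous POC result, so the effect depends on how closely venous and capillary results agree.

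The protocol also keeps leftover samples for repeat testing to settle discordant results, without saying that the recorded RT-PCR call stands.

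**3. The plan's own precision figure**

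Half-width = 1.96 × √(p(1 − p)/n).

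- n = 90, p = 0.90: 6.2 points (stated 6%).
- n = 50, p = 0.90: 8.3 points (stated 8%).

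Both reproduce after rounding and serve here only as a yardstick.

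**4. Illustration of size**

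Inputs: 90 RT-PCR positives with valid POC results and 90% sensitivity (Power analysis), giving 81 true positives and 9 false negatives. The number of re-calls, k, is my assumption; the protocol gives no figure. A false negative re-called RT-PCR negative leaves the denominator, so sensitivity = 81/(90 − k).

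| k | Sensitivity | Shift |
| --- | --- | --- |
| 0 | 81/90 = 90.0% | – |
| 1 | 81/89 = 91.0% | +1.0 |
| 2 | 81/88 = 92.0% | +2.0 |
| 3 | 81/87 = 93.1% | +3.1 |

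Re-calling a false positive as RT-PCR positive adds one to numerator and denominator: 82/91 = 90.1%, a shift of 0.1 point. That kind of re-call acts mainly on specificity.

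With the fallback of 50 positives, 45/50 = 90.0% becomes 45/49 = 91.8% for k = 1 and 45/47 = 95.7% for k = 3. The pilot has the same scale: 200 specimens at 3:1 give 200/4 = 50 positives. There a single re-call takes 45/50, which does not exceed 90%, to 91.8%, which does.

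**The case against.** **The conditional wording reflects a real constraint.** The reference laboratories are run by outside bodies, set their own PCR protocol, and do RT-PCR as clinical routine. With one operator, blinding in both directions cannot be had by ordering alone. This stands: unconditional two-way blinding may need a second person, so it should not be presented as free.

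**The order may be a default with an exception, not a contradiction.** Both versions appear in the same paragraph, and the second is introduced as depending on workflow. That is a fair reading. But the Clinical substudy text carries no such exception, and the exception is what creates the exposure.

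**The size is conjecture.** Also fair. One to three of 9 is 11% to 33% of the false negatives. Only specimens with POC run before or during RT-PCR, and an unblinded operator, are at risk. The protocol states no borderline zone or repeat rule. Ct values are recorded, so low-signal calls can be examined afterwards, although that would not show what the operator knew when making the call. A substudy SOP that is not shown may deal with the matter, but it would have to override a condition the protocol states.

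**Stronger readings that do not hold.** A reader might infer that the headline Aim 1 result is directly inflated; for fingerprick tested at the site the link is only indirect. A reader might also infer that POC results will steer care. No text directs that, and the ban is restated right after the blinding sentence. The most that can be said is that a POC-influenced RT-PCR call would carry the POC result into management by an unintended path. Nor does every altered call move sensitivity by a point, as the false-positive case shows.

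**Conclusion.** The concern stands as a correctable design weakness. The protocol permits the reference standard to be called with the laboratory POC result known; it does not show that this will happen. Under the assumed 1 to 3 re-called false negatives among 90 positives, sensitivity rises by 1.0 to 3.1 points, the upper end being about half the stated 6% margin. With no re-calls the bias is zero. The shift matters because the hypothesis is sensitivity above 90% while true performance is expected at about 85–95%, so a few calls near the threshold could change the conclusion. The direct exposure is confined to the venous result, the pilot and any fingerprick sample tested in the laboratory.

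**What to change.** 1. Reconcile the Central Reference Laboratory text with the data-collection text on the order of the two tests, for both substudy and pilot.
2. In the data-collection section and the pilot description, require that the laboratory POC result be recorded on its own form and withheld from RT-PCR operators until the RT-PCR result and Ct value are recorded, wherever different operators run the two tests.
3. State that no RT-PCR run is repeated or re-called because of a POC result. This follows from the protocol's own rule that POC results do not enter care.
4. Where one operator must run both tests, record test order and blinding status for each specimen, and report accuracy restricted to specimens with blinded RT-PCR as a sensitivity analysis.

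The cost is protocol and SOP wording, a little extra recording, a short delay in sharing laboratory POC results, and a smaller sample in the sensitivity analysis. The enrolment target does not change. Items 1 to 4 need no second operator; full two-way blinding in a single-operator laboratory would, and is not asked for here.
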